## Abstract

**Background**: Tuberculous meningitis (TBM) has 44% (95%CI 35-52%) in-hospital mortality with standard therapy in Uganda. Rifampicin, the cornerstone of TB therapy, has 70% oral bioavailability and ~10-20% cerebrospinal fluid (CSF) penetration.  With current WHO-recommended TB treatment containing 8-12mg/kg rifampicin, CSF rifampicin exposures frequently fall below the minimal inhibitory concentration for
*M. tuberculosis*. Two Indonesian phase II studies, the first investigating intravenous rifampicin 600mg and the second oral rifampicin ~30mg/kg, found the interventions were safe and resulted in significantly increased CSF rifampicin exposures and a reduction in 6-month mortality in the investigational arms. Whether such improvements can be replicated in an HIV-positive population remains to be determined.

**Protocol**: We will perform a phase II, open-label randomised controlled trial, comparing higher-dose oral and intravenous rifampicin with current standard of care in a predominantly HIV-positive population. Participants will be allocated to one of three parallel arms (I:I:I): (i) intravenous rifampicin 20mg/kg for 2-weeks followed by oral rifampicin 35mg/kg for 6-weeks; (ii) oral rifampicin 35mg/kg for 8-weeks; (iii) standard of care, oral rifampicin 10mg/kg/day for 8-weeks. Primary endpoints will be: (i) pharmacokinetic parameters in plasma and CSF; (ii) safety. We will also examine the effect of higher-dose rifampicin on survival time, neurological outcomes and incidence of immune reconstitution inflammatory syndrome. We will enrol 60 adults with suspected TBM, from two hospitals in Uganda, with follow-up to 6 months post-enrolment.

**Discussion**: HIV co-infection affects the bioavailability of rifampicin in the initial days of therapy, risk of drug toxicity and drug interactions, and ultimately mortality from TBM. Our study aims to demonstrate, in a predominantly HIV-positive population, the safety and pharmacokinetic superiority of one or both investigational arms compared to current standard of care. The most favourable dose may ultimately be taken forward into an adequately powered phase III trial.

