### Rifampicin in TBM

Rifampicin is the cornerstone drug in the treatment of TBM, as evidenced by the fact that those infected with rifampicin-resistant
*Mycobacterium tuberculosis* (
*M.tb*) strains have a near-universal fatal outcome, even with treatment with second-line drugs in resource-rich settings
^5,
13,
14^. Mortality is not nearly so high in patients with isoniazid mono-resistant TBM
^6^.

In addition to male sex and low body weight, which are associated with more rapid drug clearance
^15^, malabsorption may contribute to reduced systemic drug bioavailability in HIV-infected persons
^16–
21^. A recent comprehensive meta-analysis of rifampicin pharmacokinetics confirmed that during the initial days of TB treatment rifampicin total plasma exposure to rifampicin is reduced in HIV co-infected adults (AUC 37.2mg.h/L in HIV-positive versus 56.7mg.h/L in HIV-negative, p=0.003). Interestingly, this association did not persist in steady-state (>7 days on therapy, once saturation of first-pass metabolism and the establishment of metabolic autoinduction is well established)
^22^. Lower plasma levels of antituberculous agents are predictive of poorer outcomes in pulmonary TB
^23^, thus the lower plasma levels of rifampicin seen in HIV-positive individuals in the initial days of TBM therapy may be particularly relevant in TB meningitis, which carries a high early mortality. Specific factors that potentially play a role in reduced bioavailability include HIV-related enteric infections
^17,
18^, HIV-associated enteropathy and chronic intestinal immune activation affecting regulation of drug transporters. Patients with TBM often present while critically ill, are vomiting and frequently receive drugs through a nasogastric tube. Such factors may further associate with reduced TB drug concentrations, which could explain the lower plasma rifampicin concentrations observed in patients with TBM compared to those with pulmonary TB taking the same dose from the same setting
^24,
25^.

Rifampicin is largely protein bound and thus has limited CSF penetration, with reported CSF concentrations often reaching 10–20% of those in plasma
^25,
26^. Suggested target concentrations of rifampicin are >8mcg/ml at the site of disease, but CSF rifampicin concentrations seldom exceeded the minimum inhibitory concentration (MIC; 0.25mcg/ml) against
*M. tuberculosis* at the standard oral adult dose (8–12mg/kg)

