***Statistical methods.*** After data cleaning, analysis will proceed according to the pre-specified analysis plan using Stata version 13. The trial will be reported in accordance with CONSORT guidelines and primary analyses will be conducted by the participant’s originally assigned group (ITT). Analyses will be conducted on individuals from both study sites together and all analyses will be adjusted for site, BMRC grade and any baseline variables associated with missingness of the analysis outcome.

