**Clinical outcomes**

Survival at 8 and 24 weeks will be calculated using the risk difference, from a generalised linear regression model adjusted for site and BMRC TBM grade. Kaplan-Meier curves will also be used to compare time to death between treatment arms, with censoring and loss to follow-up handled as previously described. Cox proportion hazards regression will be used to assess the effects of rifampicin dose, plasma/CSF rifampicin concentration, HIV, MRC severity grade and baseline GCS on survival.

When calculating time to normalization of GCS continuous-valued secondary endpoints will be compared with general linear models or Wilcoxon rank-sum tests as appropriate. Death can be considered a competing risk. χ
^2^ test will be used for comparison of proportions of patients with TBM-IRIS by intervention arm.

***Secondary analysis.*** We will explore the relationship between rifampicin exposures and clinical outcomes using a population pharmacokinetic-pharmacodynamic model. We will consider C
_max_ and AUC
_0-24h_ as the exposure variables. Survival, proportion with normalisation of conscious level and functional status (as determined by modified Rankin score) are the response variables.

***Planned subgroup analyses.*** Specified high-risk subgroups are of interest because of potential different responses to intravenous rifampicin from both an efficacy and safety perspective, and the clinical utility in future physician decision-making. With standard therapy, worse clinical outcome is associated with altered mental status, high organism burden. Subgroups of interest include:

1. TBM Diagnostic category (Definite, Probable, Possible)
^33^
2. British Medical Research Council (BMRC) TBM disease severity
^7^
3. CSF inflammation (CSF white blood cells) by tertiles4. CD4 at study entry5. ART status at study entry

***Analysis of ancillary studies.*** The results of ancillary studies will be reported separately from the main trial.

Findings of the diagnostic sub-study will be reported in line with the Standards for the Reporting of Diagnostic Accuracy studies (STARD) guidelines. Sensitivity and specificity will be calculated against a composite reference standard (any positive CSF test for
*M. tuberculosis*) and against the published uniform case definition of ‘probable’ or ‘definite’ TBM
^33^. A latent class analysis will also be performed.

The studies on brain tissue concentration at autopsy will be primarily descriptive.

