## Discussion

Tuberculous meningitis is highly fatal despite current WHO recommended therapy, particularly in HIV-positive people, who are 2–3 times more likely to die than their HIV-negative counterparts. Recent evidence from Indonesian phase II studies suggests that significantly higher dose IV or oral rifampicin enhances CNS penetration and may reduce mortality. However, there is currently no available pharmacokinetic data on high-dose rifampicin for TBM in an HIV-positive African population. Furthermore, intravenous rifampicin is not widely available so finding a bioequivalent oral dose, that reaches target levels in the CNS, is a priority.

In this phase II study we anticipate the sample size will not be sufficient to detect small differences in mortality between the treatment arms. However, the pharmacokinetic and pharmacodynamic data will be used to define optimal rifampicin dose, and route of administration in an HIV-positive population, and this will be taken forward into a larger phase III randomised controlled trial, if safe and tolerable.

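### The fixed covariate set for the primary PK comparisons leaves out HIV status, and the article plans no HIV-positive exposure estimate to support its dose statement: a modest gap in precision and support, not a bias

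*Protocol article*

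**What the plan says.** **Aim and population.** The Abstract describes a trial "comparing higher-dose oral and intravenous rifampicin with current standard of care in a predominantly HIV-positive population" and says of the earlier Indonesian findings: "Whether such improvements can be replicated in an HIV-positive population remains to be determined". The Discussion says the PK and pharmacodynamic data "will be used to define optimal rifampicin dose, and route of administration in an HIV-positive population".

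**Entry and randomisation.** The inclusion and exclusion criteria set no HIV requirement. Randomisation is stratified by site and BMRC grade only.

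**Adjustment.** Under Statistical methods, "all analyses will be adjusted for site, BMRC grade and any baseline variables associated with missingness of the analysis outcome". HIV is named as a covariate in one place, the Cox model for survival under Clinical outcomes.

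**Subgroups.** The planned list ends with "CD4 at study entry5. ART status at study entry" (the 5 is a list number). HIV status itself is not on it.

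**HIV and exposure.** The section Rifampicin in TBM gives, for the first days of treatment, "AUC 37.2mg.h/L in HIV-positive versus 56.7mg.h/L in HIV-negative, p=0.003", and adds: "Interestingly, this association did not persist in steady-state". It dates steady state from after day 7. Intensive plasma sampling is on day 2 (±1). Table 5 records HIV status at screening.

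**The concern.** The protocol identifies a baseline factor that strongly predicts early exposure and samples its primary endpoint in the window where that factor acts. It then fixes, for every analysis, a covariate set that omits it. Two things are at stake.

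- **Precision.** Variation due to HIV stays in the residual of the primary PK comparison, although the data to remove it are collected anyway.
- **Support for the conclusion.** The Discussion draws an HIV-specific conclusion on dose and route, but the planned PK contrast is an average over whatever HIV mix is enrolled. If the early deficit is partly an absorption effect, as the Introduction suggests it may be, it would act on the oral arms and not on the intravenous arm. The pooled intravenous-versus-oral ratio would then differ from the HIV-positive one. Adding a covariate would not reveal that; an HIV-positive estimate would.

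**Working it through.** **Inputs from the protocol**
- Early AUC 37.2 (HIV-positive) and 56.7 (HIV-negative) mg.h/L.
- Log Cmax difference 0.54; SD 0.36 (control) and 0.48 (experimental); 15 per group; two-sided 0.05; unequal-variance t-test; stated power 90%.
- 60 enrolled at 1:1:1, so 20 per arm.

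**Assumptions**
- The HIV-positive share p is not given; 70% to 95% is used for a predominantly HIV-positive population.
- The log base is not stated; both bases are shown.
- The plasma AUC effect of HIV is taken to apply to Cmax.
- The planning SDs are taken as within-HIV-group SDs; the alternative is in step 3.

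**Step 1. Reproduce the stated power.** SE = √((0.36² + 0.48²)/15) = √(0.36/15) = 0.155. Noncentrality = 0.54/0.155 = 3.49, with about 26 Satterthwaite degrees of freedom. Power is 91.8%, consistent with the stated 90%. At 20 per arm, SE = √(0.36/20) = 0.134 and power is 97.5%.

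**Step 2. Size of the HIV effect.** 1 − 37.2/56.7 = 34.4%. The log difference is g = ln(56.7/37.2) = 0.421, or 0.183 on log10.

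**Step 3. Cost of leaving HIV out.** An unmodelled mix adds p(1−p)g² to each arm's variance. At p = 0.7 on natural logs this is 0.21 × 0.421² = 0.037, and the SDs become 0.409 and 0.517. The SD of the shift from chance imbalance between two arms of 20 is g√(2p(1−p)/20).

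| HIV-positive share (assumed) | Power, n=15 (ln) | Power, n=20 (ln) | Imbalance SD, n=20 (ln) | Power, n=20 (log10) |
|---|---|---|---|---|
| 70% | 86.3% | 94.6% | 0.061 | 97.0% |
| 80% | 87.7% | 95.3% | 0.053 | 97.1% |
| 90% | 89.5% | 96.3% | 0.040 | 97.3% |
| 95% | 90.6% | 96.9% | 0.029 | 97.4% |
| HIV in the model | 91.8% | 97.5% | – | 97.5% |

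The imbalance SD of 0.03 to 0.06 compares with a standard error of 0.134 and a design difference of 0.54. If the planning SDs already contain HIV variation, adjustment instead raises power at 20 per arm from 97.5% to between 98.0% (95% HIV-positive) and 99.2% (70%), on natural logs. Either way the gain is at most about 3 points.

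**Step 4. Route contrast if the deficit is purely an absorption effect (assumption).** The pooled intravenous-versus-oral log ratio falls short of the HIV-positive one by (1−p) × 0.421. That is 0.042, 0.084 or 0.126 at 90%, 80% or 70% HIV-positive, so the ratio is about 4%, 8% or 12% too low. High-dose oral against control would be unaffected.

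**Step 5. How many HIV-negative participants.** 60 × (1−p) gives 3 (95%) to 18 (70%), or about 1 to 6 per arm.

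**Step 6. Precision of an HIV-positive-only contrast.** With 20p per arm, SE = √(0.36/(20p)): 0.138 at 95% and 0.160 at 70%, against 0.134 for the adjusted all-comer contrast.

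**The case against.** The strongest reply is that nothing threatens the primary result. Arms are randomised and compared on the log scale, so an HIV effect that is the same ratio in every arm cancels. The Introduction reports only such a main effect, with no HIV-by-regimen difference. Chance imbalance is ordinary sampling error. The primary hypothesis and objective do not mention HIV, and the mixed population is disclosed. All of this stands. A reader might infer that HIV mixing biases or confounds the primary exposure contrast, or that HIV should have been an entry criterion or stratum; the documents do not support either.

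The reply also notes that the CD4 and ART subgroups are looks within the HIV-positive population, since Table 5 takes CD4 only in those patients. So it would be too strong to say that HIV-positive patients are never examined separately. Those subgroups, however, are framed around efficacy and safety and do not name PK. Splitting by CD4 or ART also does not give one HIV-positive exposure contrast.

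Finally, an analysis plan not shown may add HIV, and the covariates of the population PK-PD model are unstated. That limits the point to what the article fixes: a covariate rule for all analyses that admits HIV to the primary PK comparison only through missingness. The magnitude is also soft, because a plasma AUC difference is set against a Cmax SD, and it says nothing direct about CSF.

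**Conclusion.** The point holds in a modest form. The stated covariate set omits a factor that, on the protocol's own figures, lowers early AUC by 34% in the window of the primary PK sampling. The article also plans no HIV-positive PK contrast to carry the Discussion's statement on dose and route.

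The pooled contrast is unbiased for the enrolled mix. At 20 per arm the loss is about 0.6 to 2.9 points of power (96.9% to 94.6%, against 97.5%), and 0.1 to 0.5 points on log10. This rests on the assumed 70% to 95% HIV-positive share and on the AUC effect carrying over to Cmax. The 4% to 12% shortfall in the intravenous-versus-oral ratio depends further on a pure absorption mechanism, which the protocol raises only as a possible contributor.

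**What to change.** 1. In Statistical methods, add HIV status to the covariates of the primary PK comparisons, alongside site and BMRC grade.
2. State that each investigational-versus-control PK contrast, and the 8-week composite safety proportions, will also be reported descriptively in HIV-positive participants. Name these as the basis for the Discussion's statement about that population.
3. Do not add a formal HIV interaction or subgroup test. With perhaps 3 to 18 HIV-negative participants in all, it would tell little.

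**Cost.** Wording only: HIV status is already recorded, and no extra participants, visits or samples are needed. The downside is one more model term and a less precise HIV-positive-only estimate: its standard error is about 3% (at 95% HIV-positive) to 20% (at 70%) above that of the adjusted all-comer contrast (0.138 and 0.160 against 0.134). It should therefore be read as an estimate with its interval, not as a second test.

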### Randomisation and treatment allocation

Adults who have given consent for, and undergone, a diagnostic screening lumbar puncture and are eligible for enrolment will then be approached for enrolment consent after which they will be randomised. Randomisation will occur at study entry and must occur prior to the 4th dose of TB treatment. Participants will be randomised by a computer generated permutated block randomization algorithm of different sized blocks with a 1:1:1 randomization ratio into the three arms described above.

Randomisation will be stratified by:

1. Clinical site2. British Medical Research Council (BMRC) TBM disease grade I or II/III at time of consent

All randomised participants will initiate their allocated study TB treatment within 24 hours of randomisation, and preferably the same day. As TBM is a medical emergency, initiation of standard of care TB treatment will not be delayed whilst waiting for randomisation.

***Treatment discontinuation***. Due to the urgent need to begin TBM therapy to reduce mortality, enrolment will not be delayed whilst waiting for enrolment blood test results and participants will be replaced
*a posteriori* if baseline ALT>3x ULN. As infection with a rifampicin resistant TB strain is an exclusion criterion, all patients in whom rifampicin resistant TB is identified after randomisation may have their treatment altered as per physician judgement. Once randomised, analysis is by modified intent-to-treat (ITT).

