**Safety analysis**

The number and proportion of individuals who reported any kind of clinical grade 3-5 AE during the study period will be presented by intervention arm. Data for safety will be analysed in accordance with the ITT principle. The main analysis will be a composite safety endpoint over the 8-week intervention period:

AEs, clinical Grade 3-5 as classified by DAIDS Toxicity ScaleAll SAEsDILI, grade 3-5 (ALT >3x ULN with symptoms or 5x ULN without symptoms)Discontinuation of rifampicin for >5 days in the first 8 weeks for any cause

Time to experiencing an adverse event will be compared between treatment arms using cumulative incidence functions and a Cox proportional hazards regression model adjusted for site and BMRC TBM grade. Death will be considered a competing risk. The individual subgroups of AEs that make up the composite endpoint will be summarised. A secondary analysis of rifampicin-related toxicity (probable or definitely related, as assigned on the adverse events case record form) will be presented by intervention arm.

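### Adjustment for site and BMRC grade is promised for every analysis, but the rank-sum option for time to normal consciousness and the chi-square test for TBM-IRIS, as named, do not adjust

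*Protocol article*

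**What the plan says.** All references are to the protocol article.

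- **Randomisation and treatment allocation.** Participants are allocated in permuted blocks "with a 1:1:1 randomization ratio into the three arms described above". The strata are clinical site and "British Medical Research Council (BMRC) TBM disease grade I or II/III at time of consent".
- **Statistical methods.** The general rule has no exception: "all analyses will be adjusted for site, BMRC grade and any baseline variables associated with missingness of the analysis outcome".
- **Clinical outcomes, time to normal consciousness.** Here "continuous-valued secondary endpoints will be compared with general linear models or Wilcoxon rank-sum tests as appropriate". The section adds that death can be treated as a competing risk.
- **Clinical outcomes, TBM-IRIS.** A chi-square "test will be used for comparison of proportions of patients with TBM-IRIS by intervention arm". No stratified form is mentioned.
- **Where adjustment is stated.** Mortality at 8 and 24 weeks is analysed as a risk difference "from a generalised linear regression model adjusted for site and BMRC TBM grade". The composite safety endpoint is analysed with "a Cox proportional hazards regression model adjusted for site and BMRC TBM grade".

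**The concern.** A plain rank-sum test and a plain chi-square test have no place for site or grade. If they are run as named, the general rule is broken. If the general rule is followed, they cannot be run as named. The authors do write the adjustment out for the safety and mortality models, so a reader cannot assume that the bare tests are meant in stratified form.

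For time to GCS normalisation, the words "general linear models or Wilcoxon rank-sum tests as appropriate" leave the choice open between a method that can honour the rule and one that cannot. No criterion for choosing is given, and the trial is open-label.

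The second issue is efficiency. Stratified randomisation balances the arms on grade. If grade predicts outcome, a test that ignores it uses a variance that is too large for the comparison being made. Its true type I error falls below the nominal level and power can be lost. Grade is plausibly prognostic here: it is a severity grade, the endpoint is the number of days to a sustained GCS of 15, and the section on planned subgroups links altered mental status to worse outcome.

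**Working it through.** **1. The plan's own figures.** No power is stated for the rank-sum or chi-square analyses, so there is nothing to reproduce for them. The stated PK power is 90% with n = 15 per group, a log-scale difference of 0.54 and SDs of 0.36 and 0.48. The standard error is √((0.36² + 0.48²)/15) = √(0.36/15) = 0.155. The noncentrality is 0.54/0.155 = 3.49 on about 26 Satterthwaite degrees of freedom, which gives 91.8% power. The figure reproduces within 2 points and this point does not touch it.

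**2. Rule and named method, side by side.**

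| Analysis | Named method | Site and grade? |
|---|---|---|
| Composite safety | Cox model | Stated |
| Mortality, 8 and 24 weeks | Generalised linear model | Stated |
| Time to GCS normalisation | General linear model | Possible, so the rule can be met |
| Time to GCS normalisation | Rank-sum test | Not possible as named |
| TBM-IRIS | Chi-square test | Not possible as named |

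**3. Rank-sum test: size of the effect.** The document does not give the prognostic strength, so it is varied. Assumptions: 20 v 20, four site-by-grade strata of 6, 14, 6 and 14 with equal allocation within each, and a complete normal outcome with total within-arm SD 1. Grade carries a share R² of that variance. The arm effect is 0.9 SD, the level is two-sided 5%, and there are 4,000 runs per setting. The model is

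y = b·grade + √(1 − R²)·e + 0.9·arm, with b = √(R²/0.21),

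where 0.21 = 0.3 × 0.7 is the variance of the grade indicator. The van Elteren weights are 1/(n + 1) per stratum.

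| R² of grade | 0 | 0.1 | 0.2 | 0.3 | 0.4 |
|---|---|---|---|---|---|
| Power, rank-sum | 78% | 78% | 78% | 80% | 82% |
| Power, van Elteren | 75% | 79% | 82% | 87% | 92% |
| Power, adjusted linear model | 80% | 83% | 87% | 91% | 95% |
| Type I error, rank-sum | 5.3% | 4.4% | 2.2% | 1.5% | 1.1% |

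Van Elteren minus rank-sum, from unrounded values, is −3.4, +0.8, +3.7, +7.0 and +9.8 points. The stratified and adjusted methods hold a type I error of about 4% to 6%. The simulation standard error of a power near 80% is √(0.8 × 0.2/4000) = 0.6 points, so the difference at R² = 0.1 is close to noise.

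The adjusted linear model beats the rank-sum test by about 5 to 13 points for R² from 0.1 to 0.4. Part of that is the advantage of a normal-theory method on normal data. Against an unadjusted t-test in the same runs (80.5%, 80.6%, 83.0% and 85.1%), adjustment alone adds about 2.5 to 10 points.

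**4. Sensitivity to scaling.** A second simulation used 6,000 runs, assumed 20% in grade I, and set the arm effect at 0.9 of the residual SD.

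- Grade shift of 1 SD (R² = 0.16/1.16 = 14%): power 71% rank-sum v 73% van Elteren; type I error 3.3% v 4.8%.
- Grade shift of 2 SD (R² = 0.64/1.64 = 39%): power 59% v 74%; type I error 1.6% v 4.7%.

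The direction is the same. The larger gap of 15 points arises because the effect is smaller relative to the total SD.

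**5. Chi-square test for TBM-IRIS.** Same strata, treatment log odds ratio −1.8, grade log odds ratio 0, 1 or 2 (the last an odds ratio of e² = 7.4), and two base rates. Power of chi-square v Cochran-Mantel-Haenszel:

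- higher base rate: 59 v 59, 58 v 59 and 58 v 60% (the last gap is 1.3 points before rounding);
- lower base rate: 30 v 30, 31 v 31 and 35 v 35%.

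The loss is about 0 to 1 point.

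**The case against.** The strongest objection is that the conflict is thin. A general linear model is named first for the GCS endpoint and can carry both strata. The article refers to a pre-specified analysis plan that is not shown, and the exact form of a test is commonly left to such a plan. This stands in part: nobody is bound to use the rank-sum test. It does not remove the conflict, because both sentences are in this document, the rule has no exception, and TBM-IRIS has no adjustable alternative.

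The simulation is also only a rough guide. It uses complete normal outcomes, whereas the endpoint is a time that many participants may never reach: the sample-size section assumes that only 40% of controls survive 8 weeks. Participants who enter with normal consciousness would have little or no time to recover. The percentages therefore show direction and rough scale and do not predict this trial's power. This stands in full.

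A stratified test would still omit the baseline predictors of missingness that the same rule requires. That also stands, and the fix allows for it.

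Two stronger readings are tempting and are not supported. A reader might infer that the plan loses power generally by ignoring its strata. The mortality and safety models adjust, the chi-square loss is negligible, and the rank-sum loss depends on an unstated prognostic strength. A reader might also count the Kaplan-Meier curves as an unadjusted test. No test is attached to them in the Clinical outcomes section, where they sit beside an adjusted risk-difference model and a Cox model that includes severity grade.

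**Conclusion.** The inconsistency holds and is visible in the article alone. The rule of adjustment in all analyses cannot be met by the rank-sum option for time to GCS normalisation or by the chi-square test for TBM-IRIS.

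The consequence is modest. For the GCS endpoint, an unstratified rank-sum test would be conservative if grade is prognostic. It could cost about 1 to 10 points of power against van Elteren at 10% to 40% of variance explained (15 points in the most adverse setting run), and would gain about 3 points if grade explains nothing. These figures rest on assumed stratum sizes, an assumed arm effect and an uncensored normal outcome. For TBM-IRIS the point is consistency only.

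Both endpoints are secondary. The error runs towards too few rejections, so it creates no false positives. The PK sample size and the safety and mortality analyses are unaffected.

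**What to change.** Make the Clinical outcomes section agree with the Statistical methods section.

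- **Time to GCS normalisation.** Replace the plain rank-sum option with one named analysis that is adjusted for, or stratified by, site and BMRC grade. A time-to-event model with death as a competing risk suits the endpoint best. If a rank test is kept, use van Elteren and state how deaths are ranked or handled, since the test does not do this by itself.
- **TBM-IRIS.** Use a Cochran-Mantel-Haenszel test, a stratified exact test, or a regression adjusted for site and grade.
- **General rule.** If stratified tests are chosen, say that adjustment for predictors of missingness applies to the regression models only, because such tests cannot carry those variables.

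The cost is wording: both strata are recorded at randomisation and no new data are needed. The statistical price is about 3 points of power for van Elteren if grade turns out not to be prognostic. The change should be made before outcome data are reviewed by arm.
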